## 2.4. Adverse effects

We expect no adverse health effect from this intervention, except possibly for deterioration in depression (and, ultimately, suicide). We will provide the emergency phone call number at the central office, should any serious suicidal wish occurs. The clinical research coordinator (CRC), who is a clinical psychologist [name], will then deal with the emergency call first by herself, and then consult with the telephone counselor in charge and/or the clinical supervisors ([name]) to provide appropriate care. Any indirect information regarding depressive deterioration and/or suicidal ideation/attempts from any source will be fed into the CRC and will be discussed with the clinical supervisors and the individually and clinically most appropriate course of action will be taken.

We will measure deterioration in depression in our primary and secondary outcomes. We will measure suicidal attempt, completed suicide and hospitalization at 15-month follow-up. We will not implement “stopping decision rules” for this study, because we will not have a sample large enough to determine whether adverse events are clearly related to study participation or if outcome data are sufficient to answer our primary study questions prior to enrollment of the full sample. [name], the Principal Investigator, will be responsible for all the decisions. [name] will be available for review of all instances of reported adverse effects and suicide risk within 24 hours. When he is not available to fulfill this role because of travel or other obligations, [name] or another designated clinical investigator will be appointed to monitor participant safety.

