## 2.2. Secondary questions

Secondary outcomes will include:

1. At 4 months post-randomization
   1. depression severity as measured by K6
   2. client satisfaction　[VAS for satisfaction with the company’s support for mental stress, and a detailed ad hoc questionnaire for those who received telephone CBT]
2. At 15 months post-randomization
   1. depression severity [BD12 and K6]
   2. work performance
      1. “Effective hours worked” for the past month [HPQ]
      2. Job retention: has the person quit his/her job by 15 months post-randomization [yes/no, if yes when did the participant quit the job? The latter information is important for survival analysis.]
   3. client satisfaction [VAS]
   4. use of EAP services, use of health services (physical or mental), suicidal attempt, hospitalization (physical or mental) [yes/no for 15 months post randomization]
   5. time to incident major or minor depressive episode during the 15 months post randomization

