### K6

K6 is a recently developed very short (6-item) self-report questionnaire to screen for common mental disorders (Kessler et al., 2002). It is based on modern item response theory methods and consists of questions that are maximally discriminative of respondents in the 90^th^-99^th^ percentile range of the general population distribution because it is known that between 5-10% of the population suffer from mental disorders at any point in time. Only items displaying constant psychometric characteristics across sociodemographic variation are included in the final model. K6 has been found to work as well as and better than some widely used screening questionnaires (Furukawa et al., 2003; Kessler et al., 2003b). The Japanese version has been validated (Furukawa et al., in press).

We will use K6 as the initial screening instrument. In addition, we will use K6 as a process measure in the course of the telephone CBT and administer it at the beginning of every session. Together with the screening, 4-month follow-up and 15-month follow-up data (which will all be administered to the control group as well), K6 will be one of the secondary outcome measures.

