## 6.2. Termination policy

We are planning a recruitment phase of 9 months (extendable up to 12 months). We will then start the 1-year follow-up, to be implemented at 15 months after randomization for both the treatment and waiting list groups.

After this 15-month follow-up evaluation, those in the waiting list group who wish to receive telephone CBT can receive telephone CBT.

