### 8.2.2. Data and Safety Monitoring Board (DSMB)

The DSMB will consist of the CRC, [name] (statistical consultant), the two company representatives and a scientific colleague of [name] who is familiar with clinical trials and is not involved in this study (person to be determined).

The DSMB will meet every 6 months after the first client is randomized. The purpose of the meeting will be to review the report prepared by the CRC.

CRC will prepare for the DSMB reports which monitor recruitment progress and data collection (e.g. % completing different follow-ups) and adverse events and their resolution..

We will prepare a free phone number for participants to call up, should they have any suicidal ideation and other significant worsening of their depression. (Cf. 2.4. Adverse events)

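### Suicide attempts and hospitalisations are first asked about at month 15, so the DSMB's month-6 and month-12 reviews rest on spontaneous reports that are likely to be uneven between arms

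*Protocol*

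**What the plan says.** Section 2.4 names worsening depression, and ultimately suicide, as the only harm that might be expected. It then states: "We will measure suicidal attempt, completed suicide and hospitalization at 15-month follow-up". Section 2.2 places the matching items under month 15 only, as a single answer for the whole period: "suicidal attempt, hospitalization (physical or mental) [yes/no for 15 months post randomization". The month-4 list in that section has K6 and client satisfaction, but none of these items.

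Before month 15, three things bear on safety:

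- **Spontaneous reports.** There is an emergency line, and "Any indirect information regarding depressive deterioration and/or suicidal ideation/attempts from any source will be fed into the CRC". Reported adverse effects and suicide risk are open to review by a clinical investigator within 24 hours. Section 5.2.1 makes the hotline available to all participants.
- **Symptom scores.** Section 2.4 says: "We will measure deterioration in depression in our primary and secondary outcomes". That means BDI2 and K6 at month 4, in both arms.
- **Session scores, CBT arm only.** Section 5.1 says: "we will use K6 as a process measure in the course of the telephone CBT and administer it at the beginning of every session". Section 4.3 adds K6 thresholds that trigger a notice to the therapist and supervisor.

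On oversight, Section 8.2.2 says: "The DSMB will meet every 6 months after the first client is randomized". The CRC prepares the board's report, which covers recruitment, data collection, and adverse events with their resolution. Symptom scores are not listed. On membership: "The DSMB will consist of the CRC, [name] (statistical consultant), the two company representatives", plus one outside colleague still to be chosen. Section 6.2 sets the length of intake: "We are planning a recruitment phase of 9 months (extendable up to 12 months").

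**The concern.** The board's schedule and the safety questions do not line up. The board meets at months 6 and 12, while people are being enrolled and treated, but the first direct question about attempts or hospital admission falls at month 15. Until then the board sees what happens to be reported, and the chance of a report depends on how much contact a participant has with the study. The allocated treatment itself sets that contact.

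A raised count in the CBT arm could simply reflect more conversations, and a low count among controls could reflect silence. A single yes/no answer covering 15 months also relies on long recall from those who return the form. Completed suicide is promised in Section 2.4, but it is absent from the Section 2.2 item list and cannot be captured by a mailed self-report.

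A secondary matter is who reviews the report. The CRC writes it and also sits on the board that receives it. The company's representatives would receive adverse-event reports concerning the company's own employees.

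**Working it through.** The protocol gives no figure for safety coverage, so the check is a calendar count with month 0 as the first randomisation.

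**Inputs**

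- N = 297, as 99 CBT and 198 control (Section 3.2). This reproduces: control n = 3 × (1.960 + 1.282)² / 0.4² = 197.0, taken up to 198, with 99 active; power at 198 and 99 is 0.901. It serves here only as a head count.
- Recruitment length R = 9 or 12 months (Section 6.2).
- DSMB meetings at t = 6, 12 and 18 (Section 8.2.2).
- Questionnaires due at lag L = 4 and 15 months (Section 5.3.1).
- Month-4 completion of 90% (Section 3.2).
- Assumption: even accrual over R.

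**Formula.** Number past lag L at time t = N × min(max(t − L, 0), R) / R. L = 0 gives the number randomised.

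| Meeting | R | Randomised | Past month 4 | Past month 15 |
|---|---|---|---|---|
| 6 | 9 | 198 | 66 | 0 |
| 6 | 12 | about 148 | about 50 | 0 |
| 12 | 9 | 297 | 264 | 0 |
| 12 | 12 | 297 | 198 | 0 |
| 18 | 9 | 297 | 297 | 99 |
| 18 | 12 | 297 | 297 | about 74 |

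The last column is the plan as written: nobody asked at months 6 and 12, and the first answers at month 18, after intake has closed. Follow-up accrued without those questions is the number randomised times mean time since randomisation:

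- Month 6: 198 × 3 = 594 person-months (R = 9), or 148.5 × 3 = about 446 (R = 12).
- Month 12: 297 × 7.5 = about 2,228 person-months (R = 9), or 297 × 6 = 1,782 (R = 12).

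**Coverage if the items were also asked at month 4.** At month 12 it is 264/297 = 8/9 = 89% (R = 9) or 198/297 = 8/12 = 67% (R = 12). With 90% responding, that is 0.9 × 264 = about 238 (80% of 297) or 0.9 × 198 = about 178 (60%). At month 6 it is one third of those then randomised (66/198). Section 5.3.1 allows two weeks, a second mailing and then a call. If that took one month in all (an assumption), month-12 coverage before non-response would be 7/9 = 78% or 7/12 = 58%.

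**Contact by arm before month 4.** The CBT arm has eight sessions (Section 4.1), with a K6 at the start of each. The control arm, two thirds of the sample, has no scheduled assessment. Both have the hotline, but using it depends on the participant.

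**Could the added items support a comparison of arms?** With R = 9, the 264 at month 12 split 1:2 into 88 and 176. The documents give no event rate. Assuming 0.5% to 2% over four months, the expected events are 0.4 to 1.8 (CBT) and 0.9 to 3.5 (control). No useful test can be built on that.

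**Board.** The members number 1 (CRC) + 1 (statistical consultant) + 2 (company) + 1 (outside colleague) = 5. Only the last is described as not involved in the study. Without the CRC and the company representatives, 5 − 3 = 2 remain.

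**The case against.** The strongest reply is that the trial already watches for the harm it expects. Deterioration is measured at month 4 by BDI2 and K6 in both arms, and these scores begin to arrive during recruitment. All participants have the hotline, and reported events can be reviewed within 24 hours. Section 2.4 declines stopping rules because the sample is too small to attribute events, and Section 6.1.1 plans no interim analysis. On this view, earlier event data would change little.

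Most of that stands, and it limits the point. A reader might infer that there are no systematic safety data during recruitment; the month-4 scores show otherwise. A reader might also infer that month-4 items would let the board compare harm between arms in time to act; the expected counts above do not support that. What remains is that Section 8.2.2 does not list the symptom scores in the board's report, and that attempts and admissions are not asked about until month 15. Section 8.2.2 does not exclude the scores either, so supplying them would be a clarification rather than a reversal.

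On membership, a reader might infer that employees will hide suicidality or service use because their employer is on the board, biasing the outcomes. The documents do not show this. Section 3.3.3 has data handled by number, with the identifying list open to the CRC only. Nothing says that the board sees identifiable cases or that participants know who sits on it. The membership point therefore rests on independence of review, not on a demonstrated bias.

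**Conclusion.** The point holds in a limited form. For suicide attempts and hospitalisations, the DSMB has no systematically collected data at its month-6 and month-12 meetings, when about 148 to 198 and then all 297 participants have been randomised. The zero follows from the protocol's own dates; the head counts assume even accrual to 297. That spontaneous capture is fuller in the CBT arm is a likely consequence of unequal contact, not a measured difference. Month-4 items would reach about 67% to 89% of participants by the month-12 meeting (12- to 9-month intake), less with mailing lag and about 10% non-response.

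The benefit is earlier and more even detection with shorter recall. The primary analysis is unaffected, and the plan contains no error of calculation here. Board composition is a secondary point.

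**What to change.** 1. Add the existing month-15 yes/no items (suicide attempt, hospitalisation, use of health services) to the month-4 mailing in both arms, worded for the time since randomisation.
2. When the CRC telephones non-responders, record the reason for non-response, including death, at months 4 and 15. This also gives completed suicide a route into the data.
3. State in Section 8.2.2 that the DSMB report tabulates by arm these items and deterioration on the month-4 BDI2 and K6, alongside spontaneous reports.
4. Have the CRC present the report without being a voting member, and give company representatives the recruitment and data-collection figures only. Two members would then remain for the safety review, one not yet chosen, so the sponsor would need to settle its composition.

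The cost is a slightly longer month-4 form, a few more lines in an existing report and the work of settling the board's membership. No new visit or assessor is needed.

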# 3. PARTICIPANTS

## 3.1. Study population

Working men and women with subthreshold depression will be selected according to the following criteria:

### 3.1.1. Inclusion criteria

1. Age 20-57 at study entry [because the retirement age is usually 60, we have to recruit the patients well before 60 in order to allow time for follow-up]
2. Men and women
3. Currently employed full-time (either regular or temporary) by the business company
4. Expected to be employed full-time for 2 years after screening
5. K6 scores greater than or equal to 9 (or 10) at screening
6. BDI2 scores greater than or equal to 10 at 2^nd^ screening (CIDI interview)

### 3.1.2. Exclusion criteria

1. Part-time employees
2. Sick leave for 6 or more days for a physical or mental condition in the past month
3. Expected to be on pregnancy leave, maternity leave or nursing leave within 2 years after screening
4. Current treatment for a mental health problem from a mental health professional
5. Major depressive episode in the past month, as ascertained by CIDI [We do not exclude dysthymia or major depression in partial remission]
6. Lifetime history of bipolar disorder, as ascertained by CIDI
7. Any substance dependence in the past 12 months, as ascertained by CIDI. [We do not exclude substance abuse.]
8. Any other current mental disorder if it constitutes the predominant aspect of the clinical presentation and requires treatment not offered in the project

We will have a registry of all the candidates at Office X and Factory Y (approximately 1200 regular or temporary employees altogether) of this company to whom we will send the invitation letter, and compare those who give the full consent to participate in the intervention trial to the original population, to examine the generalizability of our results.

## 3.2. Sample size assumptions and estimates

A systematic review of psychological treatments, mostly CBT, for subthreshold depression yielded a Cohen’s d of 0.42 (95%CI: 0.23 to 0.60) at post-test and 0.16 (95%CI: 0.02 to 0.35) at 1-year follow-up (Cuijpers et al., 2007). ( a Cohen's d of .42 indicates a treatment effect (difference between control mean and intervention mean on the outcome measure) equal to 0.42 standard deviations (where standard deviation(SD) of interest if the SD of the outcome measure)

|  |  |  | 1:1 |  | If 1:2 |  | If 1:3 |  |
| --- | --- | --- | --- | --- | --- | --- | --- | --- |
| alpha | power | Effect size | n in each cell | Total N | n in active treatment | Total N | n in active treatment | Total N |
| 0.05 | 0.90 | 0.4 | **131** | 262 | **99** | 297 | **88** | 350 |
| 0.05 | 0.80 | 0.4 | **98** | 196 |  |  |  |  |

Thus, if we randomize 99 in the intervention group and twice that many in the control group (198) for a total of 297 randomized, we will have 90% power to detect a treatment effect assuming that this difference is equal to .40 standard deviations. However, these calculations ignore dropout. We expect that 90% will complete our month 4 followup, resulting in 89 respondents in the intervention group and 178 respondents at month 4 in the control group. In this situation, we will have 90% power to detect an effect size equal to .42 SD, which is exactly equal to our best estimate of what effect we expect to see at month 4 in this trial.

At month 15, we will have inadequate power to detect treatment effects since we expect those effects to be much smaller than those seen at month 4 (only about .16 SD's). However, in order to obtain insight into the next RCT to demonstrate prophylactic effect, we will conduct 15-month follow-up. Analyses of the 15-month follow-up will be exploratory.

If we think we can recruit 300 participants, we will go for 1:2 (intervention: control) allocation. If we expect to get closer to 200 total subjects only, we will go for 1:1 allocation, because the number in the active arm is important for journal reviewers and we would then not have 100 in the intervention group under 1:2 randomization.

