## 3.3. Recruitment of participants

The company representatives and/or the principal investigator will visit study sites and meet with the employees, if possible in small groups, to explain the purpose and rough procedures of the study to increase interest for this program beforehand.

Every month CRC will send out invitation letters and questionnaires to 200 employees, of whom 50 will be candidates (K6>=9), of whom 50 will be interviewed with CIDI by [name] and [name], of whom 40 will be eligible, of whom 30 will give the final informed consent. These 30 will be randomized to active treatment (n=10) or to waiting list (n=20). Nine telephone counselors will then have to initiate telephone CBT with 1-2 clients every month.

We will repeat this process for 9 months or until we recruit 100 clients in the telephone CBT arm.

The long wait-list and unequal allocation is defensible and explained by the limited number of competent telephone counselors available. The 9 counselors can start treating only 1-2 clients every month, i.e. 3-4 clients simultaneously at any given time (because one course of telephone CBT lasts 2-3 months); in order to recruit 100 clients, this means that 9 months of recruitment will be necessary for the 9 counselors. Those on the waiting list can receive the telephone CBT only after 15 months.

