### 3.3.1. Assessment of eligibility

#### 1^st^ screening and preliminary IC

We will send out the invitation letter, written consent form, and the screening questionnaires (JCQ, HPQ, K6 and face sheet asking for the name, date of birth, sex, email address/telephone number, job category, current treatment for physical condition, current treatment for mental condition, whether he/she is currently on sick leave for any reason, and whether he/she would like to receive the feedback on the questionnaire results, candidate appointment times for CIDI) to all the workers of Office X and Factory Y of the company.

Those who consent to the screening questionnaire and interview will return the signed consent form and the screening questionnaires individually.

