### 3.3.4. Intervention allocation

We will randomize eligible subjects to intervention and control groups at a ratio of 1:2. Randomization will be stratified on three variables, namely depression severity at baseline (BDI2=<19 vs >=20), absolute presenteeism prior to baseline (6 or higher vs 5 or lower, based on the obtained median of the eligible subjects in the pilot run) and center (Office X, Factory Y, Factory Z). Assuming that subjects are recruited from 3 sites, there will be a total of 12 strata. The study statistician will prepare 12 lists of random assignments ahead of time, one for each of the 12 strata. Each list will be blocked to ensure that the ratio of intervention to control is exactly 1:2 at set intervals within each stratum. The statistician will send these lists to the research assistant who is not involved in any other aspects of the study and who will build a spreadsheet that enables concealed sequential allocation and will be responsible for keeping these lists in the safe place.

Before randomizing an individual, the CRC will make a final determination of whether or not the person is eligible to be in the randomized trial. For example, prior to randomization, we will exclude those who score too low (BDI2=<9), which may well occur because of the difference between K6 and BDI2 and due to time elapsed for screening, because those who score too low at baseline will have less room for improvement. Once the CRC determines the eligibility of the participant, she will enter his/her registration number and the stratification variables to the spreadsheet which will automatically generate the allocation according to the pre-determined random sequence. The entered variables cannot be undone in order to guarantee allocation concealment.

Those randomized to control group will be put on a waiting list and after 15 months can receive the telephone CBT if they wish to do so.

One stratification factor is BDI2>=20 and BDI2<=19. This cutoff was chosen because our previous study suggests the score ranges 14-19 to be mildly ill, 20-28 to be moderately ill and 29- to be severely ill (Hiroe et al., 2005) and because our pilot study suggested that this is about the median BDI2 value for employees with K6>=9.

Another stratification factor is presenteeism, because this will be one of our primary outcomes and it is important to make sure that some effect can be seen, when in fact there is, probably among the more disturbed people.

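### The only stated headcount yields about 180 randomised, where section 3.2's own rule gives 1:1, yet sections 3.3 and 3.3.4 fix 1:2; Factory Z's size decides whether they conflict

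*Protocol*

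**What the plan says.** Section 3.2 makes the ratio conditional. For the larger trial: "If we think we can recruit 300 participants, we will go for 1:2 (intervention: control) allocation". For the smaller one: "If we expect to get closer to 200 total subjects only, we will go for 1:1 allocation". The reason given for the second branch is that 1:2 at that total would leave fewer than 100 people in the active arm.

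Sections 3.3 and 3.3.4 treat the ratio as settled. Section 3.3.4 states: "We will randomize eligible subjects to intervention and control groups at a ratio of 1:2". Section 3.3 splits each month's intake the same way: "These 30 will be randomized to active treatment (n=10) or to waiting list (n=20". It defends the unequal split by staffing: "The long wait-list and unequal allocation is defensible and explained by the limited number of competent telephone counselors available". Recruitment runs for 9 months, or until 100 people are in the CBT arm.

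On the source population, section 3.1.2 describes a registry of candidates at "Office X and Factory Y (approximately 1200 regular or temporary employees altogether". Under the first-screening heading in section 3.3.1, invitations go "to all the workers of Office X and Factory Y of the company". Section 3.3.4, however, stratifies on "center (Office X, Factory Y, Factory Z", and its count of 12 strata assumes three sites. No headcount is given for Factory Z.

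**The concern.** The protocol holds a rule that depends on a number, and a decision taken under that rule, but never states the number. The only figure from which a reader can derive it points to the other branch.

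Two things are at stake. At a fixed total, 1:2 has less power than 1:1 and treats fewer people. At the smaller total it also leaves the active arm well short of the 100 that section 3.2 is trying to protect. In addition, the 90% power statement assumes 297 randomised, which the invited population as described cannot supply. Neither can be repaired once allocation has begun.

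**Working it through.** **Inputs.** Section 3.2: alpha 0.05 (sidedness not stated; two-sided reproduces the table), d = 0.40 for the table and 0.42 after dropout, 90% completing month 4. Section 3.3: 30 randomised per 200 invited, 200 invitations a month, 9 counselors each starting 1-2 clients a month and carrying 3-4 at once, courses of 2-3 months. Section 3.1.2: about 1200 employees.

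**1. Reproduce the plan's figures.** Active-arm size at 1:2 is (1 + 1/2)(1.96 + 1.2816)² / 0.40² = 98.5, so 99 active and 297 in total, as stated. Power is Φ(d·√(n₁n₂/(n₁+n₂)) − 1.96). For 89 v 178 at d = 0.42: 0.42 × √59.33 − 1.96 = 1.275, or 89.9%. The stated 90% holds (89.7% with the t distribution).

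**2. Expected total.** The yield is 30/200 = 15%.
- Two sites with a headcount: 1200 × 0.15 = 180, used up after 1200/200 = 6 monthly mailings.
- Section 3.3's rate for 9 months: 9 × 30 = 270, which needs 1800 invitations.
- A total of 300 needs 300/0.15 = 2000 invitations.

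The figure of 180 may be generous: section 3.3.4 removes people with BDI2 of 9 or less before randomisation, and the monthly flow shows no separate step for this.

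**3. Apply section 3.2's rule.** Reading it as whichever of 200 and 300 is nearer, the switch point is 250 randomised, or 250/0.15 ≈ 1667 employees. At 180 the rule gives 1:1; at 270 it gives 1:2. For 1:2 to follow, Factory Z must add about 1667 − 1200 = 467 employees at the same yield.

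**4. Consequence at 180 randomised, 162 completing.**

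| Ratio | Randomised (CBT v control) | Completers | Power, d = 0.42 | Power, d = 0.40 |
| --- | --- | --- | --- | --- |
| 1:2 | 60 v 120 | 54 v 108 | 71.2% | 67.0% |
| 1:1 | 90 v 90 | 81 v 81 | 76.2% | 72.1% |

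At d = 0.42 the terms are 0.42 × √36 − 1.96 = 0.56 and 0.42 × √40.5 − 1.96 = 0.713. The t-based values are 70.7% and 75.7%. The ratio is worth about 5 points. The fall from the stated figure at 1:2 is 89.9 − 71.2 ≈ 19 points. For comparison, 270 randomised at 1:2 (81 v 162 completing) gives 87.0%.

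**5. Counselor capacity under 1:1.** Starts allowed: 9 × 1-2 = 9-18 a month.
- At 200 invitations a month, 1:1 means 15 CBT starts. Concurrent load is 15 × 2/9 to 15 × 3/9 = 3.3 to 5.0 clients per counselor, which can exceed 3-4.
- With the 1200 invitations spread over 9 months (about 133 a month), 20 are randomised and 10 start CBT each month. Load is 2.2 to 3.3, and 10 is the monthly number section 3.3 already plans.

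**The case against.** The strongest reply is that the sections need not contradict each other: section 3.2 states a conditional rule, sections 3.3 and 3.3.4 record the choice, and the 1:1 branch is an editorial leftover. Section 3.3.4 assumes three sites, and section 3.3's nine months imply 270, where the rule does give 1:2. This stands in part. It shows that 1:2 may be the right reading of the rule, but not that it is, because 270 needs 1800 invitations and the protocol describes inviting only about 1200 people. The extension to 12 months in section 6.2 adds time, not employees.

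The capacity argument also stands in part. A reader might infer that 1:2 has no staffing justification at this size. At the protocol's own mailing pace that is not supported, because 1:1 could push the load above 3-4 clients per counselor. Capacity stops being a reason for 1:2 only if invitations slow to about 133 a month, a schedule the protocol does not contain.

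It is also fair that the ratio is the smaller problem. Moving to 1:1 at 180 leaves about 76% power and 90 CBT clients, still short of 90% and 100.

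Finally, a reader might take section 3.2's rule as allowing the ratio to change during recruitment, mixing two ratios in one comparison. The protocol plans no such change: section 3.3.4 has all 12 lists prepared in advance, in blocks at 1:2.

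**Conclusion.** The point holds conditionally. The population that the protocol counts and invites yields about 180 randomised; there section 3.2's rule calls for 1:1 and sections 3.3 and 3.3.4 do the opposite. It is tempting to conclude outright that the trial has the wrong ratio and loses a third of its possible CBT clients (60 instead of 90). The documents do not support that, because Factory Z is named and its size is unknown. With about 467 or more employees there, 1:2 is what the rule prescribes.

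If the frame is 1200, power at d = 0.42 is about 71% under 1:2 and about 76% under 1:1, against the stated 90%. About 5 points are due to the ratio; the rest is the shortfall in numbers. These figures assume the 15% yield at every site, 90% completion of month 4, a two-sided 0.05 test, and a switch point midway between 200 and 300.

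**What to change.** Before the first randomisation:

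1. Reconcile the participating sites in sections 3.1.2, 3.3.1 and 3.3.4, give Factory Z's headcount if it takes part, and state the expected total.
2. Apply section 3.2's rule to that total.
   - Below about 250: prepare the 12 stratum lists at 1:1, amend the 1:2 statements in sections 3.3 and 3.3.4, and spread invitations over the 9 months (about 133 a month for 1200 employees) so that CBT starts stay near 10 a month.
   - About 250 or more: keep 1:2 and delete the unused 1:1 branch from section 3.2.
3. In either case, restate power at the expected total.

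The cost is protocol wording and, under 1:1, newly generated lists. If 1:1 applies at 1200 employees, recruitment takes the full 9 months instead of about 6, and the counselors treat about 90 clients instead of 60, within the 100 already planned. No additional participants or counselors are needed. The change of ratio does not close the recruitment shortfall; restating power makes that visible.
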